### Study setting

ADOPT Online and ADOPT Treatment are multisite trials with five study centers located in four cities in Germany (Cologne, Dresden, Mannheim, Ulm). If required, additional centers will be included. ADOPT Institution is a multisite trial with six study centers located in five cities in Germany (Cologne, Dresden, Mannheim, Ulm, Neuruppin). The coordinating center for ADOPT Online is the Department of Special Education at the Faculty of Human Sciences at the University of Cologne. The coordinating center for ADOPT Treatment is the Department of Child and Adolescent Psychiatry, Psychosomatics and Psychotherapy, Medical Faculty at the University of Cologne. The coordinating center for ADOPT Institution is the Department of Child and Adolescent Psychiatry/ Psychotherapy at the University of Ulm. Patients will be treated locally at the respective study centers, with the exception of ADOPT Online, which will be provided centrally online. Responsibility for the coordination of the whole ADOPT consortium and data management is held by the Department of Child and Adolescent Psychiatry, Psychosomatics and Psychotherapy, Medical Faculty of the University of Cologne. Responsibility for monitoring lies with the Clinical Trials Center Cologne. The Institute of Medical Statistics and Computational Biology at the University Hospital Cologne (IMSB) is responsible for statistical analysis.

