### Allocation

Patients fulfilling the eligibility criteria at T1 will be centrally registered and will be randomly assigned to the treatment groups (ADOPT Online or TAU, allocation ratio 5:1; THOPAS or TAU, allocation ratio 1:1) according to permuted blocks of varying length. Randomization will be stratified by recruitment process (ADOPT Online and ADOPT Treatment), gender and study site (i.e. 20 strata altogether for ADOPT Online/ADOPT Treatment, 12 strata altogether for ADOPT Institution) and implemented as a central 24–7 Internet service (ALEA, FormsVision BV, Abcoude, NL) operated by local authorized study staff. Treatment assignments will be displayed on screen and delivered by e-mail. The randomization service will be maintained by the IMSB, University of Cologne.

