#### Predictors/moderators of treatment outcome on AD symptoms and impairment

As predictors/moderators of treatment outcome on AD symptoms and impairment, the following variables will be analyzed: (1) gender, (2) age of patients and parents/foster parents, (3) recruitment process (community cohort vs. outpatient sample; in ADOPT Online/ADOPT Treatment); (4) chronicity of AD symptoms, (5) severity of AD symptoms, (6) severity of comorbid symptoms, (7) AD symptoms and other psychopathology of the participating parent/foster parent, (8) positive and negative parenting practices, (9) receipt of social welfare assistance by the family, (10) socioeconomic status of the family/foster family, (11) early childhood neglect of the patient, (12) adverse childhood experiences of the patient, (13) family climate according to the child’s perception, (14) social support and (15) personal resources of the child. These parameters will be assessed at T1 and/or at T2. Additionally, (16) the profile of usage of the online tool (ADOPT Online) as well as (17) the implementation of treatment modules (ADOPT Treatment/ADOPT Institution) will be assessed and analyzed as predictors of treatment outcome in the intervention groups, along with (18) treatment adherence and (19) treatment fidelity in ADOPT Treatment/ADOPT Institution, both rated by the therapist, (20) the current mood of the patient (measured with the momentary assessment function of the therapy app), and (21) behavior, thoughts, emotions, and reactions of the child in therapy-relevant difficult situations (measured with the video diary function of the therapy app).

Sociodemographic variables (e.g., gender of the patient, age of patients and parents/foster parents, receipt of social welfare assistance by the family/foster family, socioeconomic status of the family/foster family) will be assessed via parent/caregiver interview at T1.

The chronicity of AD symptoms of the child will be assessed with the DADYS-PI (see above) at T1.

The severity of AD symptoms will be assessed at T2 in blinded clinical rating as well as patient, parent/caregiver and teacher rating using the DADYS-PI/questionnaires (see above).

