#### Analysis of primary endpoint

The primary (full) analysis set is derived from the ITT principle (all patients randomized with a valid baseline assessment: ADOPT Online/ADOPT Institution: T1/ADOPT Treatment: T2 and at least one follow-up measurement). The primary outcome measures “change in AD symptoms from T1 to 13 weeks post-randomization (T2)” (ADOPT Online), “change in AD symptoms from T2 to 32 weeks post-randomization (T3)” (ADOPT Treatment) and “change in AD symptoms from T1 to 32 weeks post-randomization (T2)” (ADOPT Institution) will be evaluated by an ANCOVA, with fixed effects baseline, study center, gender and treatment arm and corresponding marginal means and contrast tests (type II sums of squares). Interactions of study center and gender with treatment arm will be explored. Data from study centers with low recruitment (i.e., < 10 patients) will be pooled. The potential clustering of observations of participants by therapist or center will be investigated using multilevel modelling. Multiple imputation approaches will be taken to assess the robustness of the results. Specifically, missing values will be separately imputed by type assuming mixtures of missingness-not-at-random patterns [102]. Imputation data sets will be post-processed by multiplication with factors and addition of offsets (tipping point analysis) [103]. Proxy measures will be taken into account to ameliorate the effects of attrition.

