#### Analysis of secondary endpoints

Secondary outcomes (i.e., further time points and measures) will be analyzed along the same lines, possibly using MMRM (heterogeneous first-order autoregressive-structured covariance matrix over time) or generalized estimating equation approaches with corresponding marginal means and contrast tests (“multilevel modelling”). Time-to-dropout distributions will be summarized by the Kaplan-Meier method and compared using the (stratified) log-rank test. Adverse events will be aggregated by type, seriousness, intensity and relatedness. All efficacy and safety variables will be summarized by time point and treatment arm (mean, standard deviation, percentiles (i.e., minimum, 25th, 50th, 75th, and maximum), count, percentage). Subgroup analyses will be conducted according to recruitment process, study center and gender (expected male to female ratio of 7:3, thus, meaningful results are expected for boys and girls). Moreover, moderation, mediation and conditional process modelling [104] will be conducted based on regression and structural equations (interaction, simple slope analysis; direct/indirect effects, kappa square). All of the details, particularly regarding how to deal with missing data and attrition, will be documented in a statistical analysis plan.

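### Recruitment process is a stratification factor in ADOPT Online and ADOPT Treatment but is missing from their primary ANCOVA, so the standard error may be slightly too large

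*Protocol article*

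**What the plan says.** The Allocation section of the protocol article states: "Randomization will be stratified by recruitment process (ADOPT Online and ADOPT Treatment), gender and study site". It counts "20 strata altogether for ADOPT Online/ADOPT Treatment, 12 strata altogether for ADOPT Institution".

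The section Analysis of primary endpoint gives one ANCOVA for all three trials, "with fixed effects baseline, study center, gender and treatment arm". Recruitment process is not among the terms. The section Analysis of secondary endpoints says that further time points and measures follow the same approach, so the omission carries over.

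Recruitment process does appear elsewhere. It is the third item in the list of predictors and moderators of outcome on AD symptoms and impairment, and the secondary analyses include it: "Subgroup analyses will be conducted according to recruitment process, study center and gender".

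**The concern.** A factor used to stratify the randomisation is normally carried into the primary model. Stratification makes the arms alike on that factor, so its contribution to the outcome largely cancels from the treatment contrast. A model that omits the factor does not know this. It counts the factor's variance as residual noise and reports a standard error larger than the true sampling variation of the estimate.

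What is at stake is a confidence interval somewhat too wide, a test somewhat below its nominal 5% level, and some power that could be had at almost no cost. How much depends on what recruitment process still predicts once baseline score, center and gender are in the model.

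**Working it through.** **1. Is recruitment process really a design factor?** The Study setting section describes ADOPT Online and ADOPT Treatment as "multisite trials with five study centers located in four cities in Germany" and ADOPT Institution as a "multisite trial with six study centers located in five cities in Germany".

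- Online/Treatment: 5 centers × 2 genders × 2 recruitment routes = 20 strata, as stated.
- Institution: 6 centers × 2 genders = 12 strata, as stated.

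So the factor belongs to the first two trials only. The ANCOVA terms match the design of ADOPT Institution but not that of the other two.

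**2. Does the sample size rely on the term?** ADOPT Online is sized on a two-sample t-test with effect size 0.378 and 331 + 66 evaluable children. This gives 79.9% power, and 397/0.8 = 496.25, about the stated 497. ADOPT Treatment uses d = 0.5 and 64 per arm, which gives 80.1% power; 128 × 1.4 = 179.2, and 179.2 × 1.1/0.85 = 231.9, about the stated 232. Neither calculation contains a covariate term.

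**3. Size of the effect by formula (ADOPT Online).** Let R² be the share of the variance left after baseline, center and gender that recruitment process explains, and k = √(1 − R²). R² is an assumption; the documents give no value.

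- Reported SE / true SE without the factor = 1/k
- Actual two-sided type I error = 2Φ(−1.96/k)
- Standardised effect z = 0.378/√(1/331 + 1/66) = 0.378/0.1348 = 2.804
- Power without the factor = Φ((z − 1.96)/k)
- Power with the factor = Φ(z/k − 1.96)

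| R² | SE ratio | Type I error | Power without | Power with | Difference (points) |
|---|---|---|---|---|---|
| 0% | 1.000 | 5.0% | 80.07% | 80.07% | 0 |
| 1% | 1.005 | 4.9% | 80.19% | 80.46% | 0.3 |
| 2% | 1.010 | 4.8% | 80.31% | 80.85% | 0.5 |
| 5% | 1.026 | 4.4% | 80.68% | 82.04% | 1.4 |
| 10% | 1.054 | 3.9% | 81.32% | 84.03% | 2.7 |

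The table uses the normal approximation, so its first row is slightly above the 79.9% of the t-test.

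To read R² as a difference between the routes: with a share p in one route and a residual difference of d SD, R² = p(1 − p)d²/(1 + p(1 − p)d²). With p = 0.5 and d = 0.2 this is 1.0%; p = 0.5 and d = 0.3 gives 2.2%; p = 0.3 and d = 0.5 gives 5.0%.

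**4. Check by simulation.** Stratified permuted blocks, 397 children at 5:1 and 198 at 1:1, an assumed 40% in one route, no therapist clustering, 6,000 runs under the null. Monte Carlo error is about 1% on the SE and 0.3 points on type I error.

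| Trial | Residual difference (SD) | Mean model SE, without / with factor | Ratio |
|---|---|---|---|
| Online | 0 | 0.1348 / 0.1349 | 1.00 |
| Online | 0.3 | 0.1363 / 0.1350 | 1.01 |
| Online | 0.5 | 0.1388 / 0.1350 | 1.03 |
| Online | 0.8 | 0.1445 / 0.1351 | 1.07 |
| Treatment | 0.3 | 0.1440 / 0.1426 | 1.01 |
| Treatment | 0.5 | 0.1466 / 0.1426 | 1.03 |
| Treatment | 0.8 | 0.1526 / 0.1427 | 1.07 |

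The 0.8 SD rows lie beyond the R² range above: 1 − (0.1351/0.1445)² = 12.6%.

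The actual spread of the Online estimates hardly differed without and with the factor: 0.1362 and 0.1359, 0.1341 and 0.1337, 0.1392 and 0.1380 for differences of 0.3, 0.5 and 0.8 SD. No meaningful bias appeared. Type I error without the factor ranged from 3.6% to 5.2% over both trials. With the factor, where the true value is 5%, it ranged from 4.7% to 5.8%, which shows how noisy these rates are. The problem is therefore an overstated SE, not a noisier estimate.

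**The case against.** The strongest reply is that the stated analysis is valid as it stands. It is unbiased, any error is on the conservative side, and the sample sizes rest on unadjusted t-tests, with covariate gains treated as a bonus. All of that holds.

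The effect may also be close to nothing. Children from both routes must exceed the DADYS-PI cut-off, and the baseline score is in the model, so much of any severity difference is already absorbed. That stands too. It does not show that R² is zero: community children are picked by a screening percentile and outpatients by clinical judgment, so children with the same baseline score could change differently. The plan itself lists the route as a possible predictor.

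It could be said that the analysis plan will settle the model. But the article names the fixed effects, so the mismatch lies in what is stated.

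A reader might infer more than the documents support:

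- **That recruitment process is the most prognostic of the three factors, or that outpatients receive different usual care.** Nothing in the article says so; the TAU section does not distinguish the two groups.
- **That the different offer to outpatient TAU families after T2 makes the factor matter in ADOPT Online.** The primary outcome there is the change from T1 to T2, before that offer.
- **That effect modification by recruitment process is neglected.** The primary section says only "Interactions of study center and gender with treatment arm will be explored", but recruitment process is a listed moderator and a planned subgroup factor, and moderation modelling is planned.
- **That precision is lost in addition to the standard error being wrong.** These are one effect described twice.

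**Conclusion.** The mismatch is certain; its consequence is small and conditional. A named stratification factor is missing from the stated primary model of ADOPT Online and ADOPT Treatment. If the factor has residual prognostic value, the reported standard error is too large and the test conservative. For an assumed R² of 1% to 10%, the standard error is about 0.5% to 5% too large and ADOPT Online forgoes about 0.3 to 3 points of power. At R² = 0 nothing is lost.

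The documents do not support reading this as a threat to the validity of a positive result or as a shortfall against the planned power: without the factor, power for the planned effect stays at about 80% or slightly above.

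The conclusion rests on the assumed R² and on the balance from stratification carrying over to the children analysed.

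**What to change.** Add recruitment process (community cohort or outpatient sample) as a fixed effect to the primary ANCOVA of ADOPT Online and ADOPT Treatment, and to the secondary models that follow the same approach. State the ADOPT Institution model separately and leave it as it is. No further interaction term is needed.

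The cost is one degree of freedom and one term in the model statement. The variable is already recorded at randomisation. Sample sizes do not change. The change should be fixed before unblinding, so that no choice between two primary models arises later.

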At T1, symptoms of AD will be more intensively evaluated by clinicians’ ratings based on parent interviews conducted with the outcome measure for AD (Diagnostic Tool for Affective Dysregulation in Children – Parent Interview; DADYS-PI) ([name] et al., 2018, unpublished manuscript), which will be developed in ADOPT Epidemiology in cooperation with ADOPT Treatment. Exclusion criteria (intelligence quotient < 80; mental disorder other than comorbid conditions is the primary disorder and the main cause of AD (e.g., autism spectrum disorder); current or planned intensive behavioral therapy (ADOPT Online)/intensive psychotherapy or PMT (ADOPT Treatment/ADOPT Institution) on a weekly/biweekly basis) will also be assessed at T1/T2 (ADOPT Treatment), along with the residence of the child (ADOPT Online/ADOPT Treatment: with natural or adoptive parents; ADOPT Institution: residential care or foster care). Additionally, two healthy control groups (No AD; in ADOPT Online/ADOPT Treatment and in ADOPT Institution) will be identified via the screening and will be pursued from T1-T4 (ADOPT Online/ADOPT Treatment) and from T1-T3 (ADOPT Institution).

In ADOPT Online, children selected from the community sample and from the outpatient sample of the study centers will be randomized to TAU or ADOPT Online. Children will be reassessed after parents have had access to ADOPT Online for 3 months (T2). Families of the community cohort randomized to TAU will gain access to ADOPT Online after T2. Families of the outpatient sample randomized to TAU will be offered the choice between continuing TAU and participating in the online intervention (ADOPT Online) after T2. From T3 to T4, ADOPT Online will also pursue those children who were in the No AD group from the beginning as well as those who showed no residual AD at T2. For detailed information see Additional file 1: Trial registration ADOPT Online.

In ADOPT Treatment, children with substantial residual symptoms of AD after ADOPT Online, as rated by the clinician on the outcome measure for AD based on parent interview (DADYS-PI), will be included in ADOPT Treatment. The patients will be randomized to TAU or the psychotherapy intervention, which will comprise a modular, individual behavioral approach based on THOPAS [[name] & [name], 2018, unpublished manuscript]. For detailed information see Additional file 2: Trial registration ADOPT Treatment.

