At the main assessment points (T1-T3/T4), the primary outcome (blinded clinician-rated AD symptoms based on parent interview) and the secondary outcomes will be assessed. In ADOPT Online, information about the use of the online tool will be collected after participating parents have provided informed consent. The intermediate assessments at T1b (ADOPT Institution) and T2b (ADOPT Treatment) will only include parent- and child-report questionnaires, and no clinical interviews. During T1b/T2b, potential treatment mediators and predictors and short forms of the parent-rated AD symptoms will be assessed. In addition, the therapist in ADOPT Treatment/ADOPT Institution will complete a questionnaire to measure adherence and treatment integrity at regular intervals during the treatment.

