As the study designs of ADOPT Online and ADOPT Treatment include a stepped care process, the sample size is defined by the expected effect sizes of the ADOPT Treatment step. The effect sizes found in the reported meta-analyses of trials on the effects of mostly standardized treatments in a group format (mostly compared with waiting list control) are in the range of *d* = 0.3 to 0.6. The effect sizes of personalized individual treatments tend to be elevated, in the range of 0.6 to 0.8 [51, 98]. The planned trial will be conducted with online treatment-refractory AD and may therefore comprise a more severe group of patients, who may be harder to treat. Thus, a moderate effect size of *d* = 0.5 is expected. The two-sample *t*-test with an allocation ratio of 1:1 (THOPAS: TAU) requires 64 patients per group in order to attain a power of 80% at a two-sided significance level of 5%. A similar therapist effect (due to clustering) as in [99] yields a design effect of 1.4 (intraclass correlation 0.1, five patients per therapist on average); thus, *n* = 179 [128*1.4] patients are required [100]. Further accounting for heterogeneous cluster sizes (+ 10%) and attrition (+ 15%) yields approximately *n* = 232 patients to be randomized (*n* = 116 to THOPAS, *n* = 116 to TAU). Note that power is further increased by taking a baseline-adjusted analysis of covariance (ANCOVA)/mixed model for repeated measures (MMRM) approach for statistical analysis. We expect a male:female ratio of 7:3 [51]. Thus, the sample size of ADOPT Treatment is set at *n* = 232, with *n* = 116 in the treatment arm and *n* = 116 in the control group.

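### The ADOPT Treatment primary ANCOVA uses T2 as its only symptom score and leaves out the blinded T1 score, forgoing a probably small amount of free precision

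*Protocol article*

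**What the plan says.** Under Analysis of primary endpoint, the protocol article sets the primary model as an ANCOVA "with fixed effects baseline, study center, gender and treatment arm and corresponding marginal means and contrast tests". The same paragraph names the baseline visit for each subproject: "ADOPT Online/ADOPT Institution: T1/ADOPT Treatment: T2 and at least one follow-up measurement". In ADOPT Treatment, T2 is therefore the only symptom score in the model, alongside center and gender.

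A T1 score exists as well. Participant timeline states: "At the main assessment points (T1-T3/T4), the primary outcome (blinded clinician-rated AD symptoms based on parent interview". The Primary outcome section also places the blinded rating at T1 to T4. By the timeline, T2 comes 13 weeks after T1, randomisation to THOPAS or TAU follows T2, and T3 comes 32 weeks after T2.

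Children pass two DADYS-PI thresholds. The inclusion criteria require a score above the cut-off at T1 for ADOPT Online and at T2 for ADOPT Treatment. Trial design describes those who enter ADOPT Treatment as "children with substantial residual symptoms of AD after ADOPT Online, as rated by the clinician on the outcome measure for AD". The value of the cut-off is not given.

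Under Sample size, the article notes, without a figure, that baseline adjustment raises power further.

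**The concern.** A child randomised in ADOPT Treatment has two planned pre-randomisation readings of the outcome variable, and the model uses one. A clinician's rating of an interview is fallible, so T2 carries error and short-term fluctuation. T1 can then hold information about the child's stable level that T2 misses. If it does, leaving T1 out makes the confidence interval for the treatment contrast somewhat wider than the collected data require. A covariate fixed before randomisation does not bias the contrast. What is at stake is efficiency only, in a trial planned at 80% power.

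**Working it through.** **1. The plan's own figure.** Inputs from Sample size: "Thus, a moderate effect size of *d* = 0.5 is expected", 80% power, two-sided 5%, design effect 1.4, allowances of 10% for unequal clusters and 15% for attrition.
- The two-sample t-test (noncentral t) needs 63.8, so 64 per arm.
- 128 × 1.4 = 179.2.
- 179 × 1.1 / 0.85 = 231.6 and 179 / 0.9 / 0.85 = 234.0. The stated 232 reproduces ("with *n* = 116 in the treatment arm and *n* = 116 in the control group").
- Effective number per arm: 232 × 0.85 × 0.9 / 1.4 / 2 = 63.4, giving unadjusted power of 79.8%. No covariate gain is used in reaching 232.

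**2. Formula.** With T2 in an ANCOVA, analysing change from T2 gives the same treatment contrast as analysing T3. Adding T1 multiplies the residual variance by 1 − p², where p is the partial correlation of T1 and T3 given T2. With equal correlations r and no selection, p² = r²/(1 + r)². At r = 0.6 this is 0.36/2.56 = 14.1%. Under exact AR(1), the T1–T3 correlation is the product of the other two, so p = 0 and the gain is nil. For a fractional cut c, the equivalent number of extra children is 232 × (1/(1 − c) − 1).

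**3. What selection does.** Simulated at r = 0.6 with a cut at z = 1.28 (top 10%):
- No selection: T2 explains 36% of T3 variance, and adding T1 cuts residual variance by 14%.
- Selection at T2 only: T2 explains 9%, and adding T1 still cuts residual variance by 14%. Selecting on T2 does not alter how T1 and T3 relate given T2.
- Selection at T1 and T2: T2 explains about 8%, and adding T1 cuts residual variance by 5%. Selection on T1 restricts the added covariate itself.

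**4. Size under selection at both visits.** All correlations and the z = 1.28 cut are assumptions. Noisy selection means that entry depends on the score plus independent noise of SD 0.6. It is included because the article does not say that the entry rating and the later blinded video rating are the same.

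| Assumed correlations (T1–T2 / T2–T3 / T1–T3) | Cut in residual variance, exact / noisy selection | Equivalent children, exact / noisy |
|---|---|---|
| AR(1): 0.60 / 0.60 / 0.36 | 0% / 0% | 0 / 0 |
| Decay: 0.60 / 0.55 / 0.45 | 1.1% / 1.8% | 3 / 4 |
| Decay: 0.65 / 0.60 / 0.50 | 1.2% / 1.8% | 3 / 4 |
| Decay: 0.70 / 0.60 / 0.50 | 0.7% / 1.2% | 2 / 3 |
| Trait 30%, state 40%, error 30%; state correlation 0.8 per 13 weeks: 0.62 / 0.53 / 0.48 | 2.0% / 3.2% | 5 / 8 |
| Equal, 0.5 | 3.6% / 5.7% | 9 / 14 |
| Equal, 0.6 | 5.0% / 8.4% | 12 / 21 |
| Equal, 0.7 | 7.4% / 11.0% | 19 / 29 |

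A separate run of the equal-correlation case with exact selection gave 3.4% at r = 0.5, or 232 × (1/0.966 − 1) = 8 children. That is the lower end of the range quoted for equal correlations.

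**5. Power.** Take 63.4 effective children per arm and d = 0.5 relative to the SD in the selected sample. With exact selection and equal correlations of 0.5 / 0.6 / 0.7, power moves from 81.6% to 82.9%, 82.7% to 84.5%, and 84.6% to 87.2%. In the three decay rows the gain is under half a percentage point.

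**The case against.** The strongest reply is that nothing here is an error. Adjusting for the last score before randomisation is standard and unbiased. The sample size rests on an unadjusted t-test with a design effect, and the remark on extra power is an unquantified aside. That stands.

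The second reply is that the gain may be negligible. T1 lies 45 weeks before T3 (13 + 32) and T2 only 32. Most families also receive the online programme between T1 and T2, given the 5:1 allocation, so T1 probably correlates with T3 less than T2 does. The article itself names a heterogeneous first-order autoregressive structure, though only for a possible secondary mixed model. This also stands, and it is why the range starts at zero. An exact AR(1) pattern in observed scores would, however, require essentially error-free ratings, which is unlikely for a newly developed interview scale.

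A third reply is that covariates can be left to the statistical analysis plan. The article defers detail to that plan, especially on missing data, but it does state the primary covariate list, and T1 is not on it.

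A reader might infer that T1 is needed because selection on T2 has weakened T2 as a covariate. The documents do not support that reasoning. Selection at T2 does lower what T2 explains, but it leaves T1's relative contribution unchanged, and the entry threshold at T1 reduces it. The top-10% rule in the article also belongs to the screening data. Applying it to the DADYS-PI is an assumption.

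**Conclusion.** The point holds as a small efficiency gain. The ADOPT Treatment primary model has T2 as its only symptom score, although a blinded T1 score is planned before that randomisation. The cut in residual variance from adding T1 is 0% under exact AR(1), about 1–3% (roughly 2 to 8 of 232 children) with decaying correlations or a trait-plus-state model, and about 3–11% (roughly 8 to 29 children) with equal correlations of 0.5–0.7. The last two ranges assume top-10% selection on the DADYS-PI at T1 and T2. Neither the correlations nor the cut-off is documented, so no single figure can be defended, and the lower part of the range is at least as plausible as the upper.

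It would be too strong to conclude that the planned ANCOVA is biased, that the trial is underpowered, or that the statement on baseline adjustment is wrong. The analysis is valid, and 232 reproduces without any covariate gain. Priority is low.

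**What to change.** Under Analysis of primary endpoint, state for ADOPT Treatment that the fixed effects are blinded DADYS-PI at T2, blinded DADYS-PI at T1, study center, gender and treatment arm. A missing T1 value, which should be rare because T1 eligibility rests on a DADYS-PI rating, can be replaced by the overall mean, computed without regard to arm. Treat secondary outcomes in ADOPT Treatment the same way only where the measure is taken at both T1 and T2. Satisfaction with ADOPT Treatment is first rated at T3 and has no such counterpart.

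The change should be fixed before any unblinded analysis, since a covariate added later would look data-driven. It costs one added covariate and one degree of freedom, with no new data.

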The planned trial will be conducted with children in OHC, who presumably have a higher comorbidity load and may therefore constitute a more severe group of patients, who may be harder to treat. Thus, a moderate effect size of *d* = 0.6 is expected. The two-sample t-test with an allocation ratio of 1:1 (THOPAS:TAU) requires 45 patients per group to attain a power of 80% at a two-sided significance level of 5%. A similar therapist effect (due to clustering) as in [99] yields a design effect of 1.4 (intraclass correlation 0.1, five patients per therapist on average); thus, *n* = 126 [≈(45 + 45)*1.4] patients are required. Further accounting for heterogeneous cluster sizes (+ 10%) and attrition (+ 15%) yields about *n* = 166 [≈126/0.9/0.85] patients to be randomized (*n* = 83 to THOPAS, *n* = 83 to TAU). Based on previous experience, we expect that 664 patients need to be screened for eligibility (i.e. only 25% are eligible). Note that power is further increased by taking a baseline-adjusted ANCOVA/ MMRM approach for statistical analysis. We expect a male:female ratio of 7:3 [39].

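### The primary ANCOVA for ADOPT Treatment and ADOPT Institution has no therapist term, so under the therapist ICC of 0.1 used for the sample size it rejects more often than the stated 5%

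*Protocol article*

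**What the plan says.** Under Analysis of primary endpoint, the change in AD symptoms in all three trials "will be evaluated by an ANCOVA, with fixed effects baseline, study center, gender and treatment arm", tested through marginal means and contrasts. No therapist term and no cluster-adjusted variance is named. Clustering appears later in the same paragraph: "The potential clustering of observations of participants by therapist or center will be investigated using multilevel modelling". That sentence stands among explored interactions, pooling of small centers and robustness checks by imputation. Nothing says that the multilevel result replaces the ANCOVA result, or which prevails if they differ.

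Under Sample size, a therapist effect taken from a cited study "yields a design effect of 1.4 (intraclass correlation 0.1, five patients per therapist on average"). The same figures are used for ADOPT Treatment and for ADOPT Institution. Both then add 10% for unequal cluster sizes and 15% for attrition, giving 232 and 166 children.

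Two other sections matter. Inclusion and exclusion criteria describes trained therapists who administer THOPAS. Study setting says that treatment takes place locally at the study centers, so THOPAS therapists are nested within centers.

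**The concern.** The sample size and the primary test make opposite assumptions about the same data. The first treats children of one therapist as correlated and recruits 40% more of them for that reason. The second treats them as independent.

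The fixed center effect does not repair this. Several therapists work within a center, and a THOPAS therapist's children are all in one arm. Differences between therapists therefore feed directly into the THOPAS-TAU contrast, while the ANCOVA residual variance divided by the number of children understates that contribution.

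At stake is the confirmatory claim of two trials. If the planning ICC is right, the p-value is too small, the 95% interval too narrow and the 5% level not held. Leaving clustering to be examined alongside also leaves open, until results are known, which model carries the conclusion.

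**Working it through.** **Inputs (protocol article, Sample size unless noted).** ICC 0.1; five children per therapist; allocation 1:1 (Allocation); two-sided 5% and 80% power; d = 0.5 (Treatment) and d = 0.6 (Institution); children to be assessed at the primary time point: 198 (Treatment, T3) and 140 (Institution, T2).

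**Step 1. The plan's own figures reproduce.**
- Design effect: 1 + (5 − 1) × 0.1 = 1.4.
- Treatment: 64 per group by the t-test (power 80.1%). 128 × 1.4 = 179.2, and 179.2 × 1.1 / 0.85 = 231.9, so 232.
- Institution: 45 per group (power 80.4%). 90 × 1.4 = 126, and 126 / 0.9 / 0.85 = 164.7, so 166 with equal arms.

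The therapist effect is thus fully built into both numbers.

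**Step 2. Type I error of a test that ignores the clustering.** If the true variance of the arm difference is V times the variance the model uses, the two-sided error is 2 × [1 − Φ(1.96/√V)].

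With clustering in THOPAS only and equal arms, V = (DE + 1)/2. With equal clustering in both arms, V = DE.

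| Case | DE | THOPAS only: V | Error | Both arms: error |
|---|---|---|---|---|
| ICC 0.1, 5 per therapist | 1.40 | 1.20 | 7.4% | 9.8% |
| As above, DE × 1.1 for unequal clusters | 1.54 | 1.27 | 8.2% | 11.4% |
| ICC 0.1, 4.25 per therapist (5 less 15% attrition) | 1.325 | 1.16 | 6.9% | 8.9% |

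Coverage of the 95% interval is one minus the error, for example 92.6% in the first row for THOPAS-only clustering.

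Sensitivity to the ICC, THOPAS only: at 0.05, DE = 1.2, V = 1.10, error about 6.2%. At 0.15, DE = 1.6, V = 1.30, error about 8.6%; with the further factor 1.1, DE = 1.76, V = 1.38, error about 9.5%.

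**Step 3. Simulation of the stated ANCOVA under no treatment effect.** Model terms were baseline, center, gender and arm. Therapists were nested in five centers (Treatment) or six (Institution), with about five children each.

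| Scenario | Treatment | Institution |
|---|---|---|
| ICC 0.1, THOPAS only | 7.0% to 7.6% | 6.2% to 7.3% |
| ICC 0.1, both arms | about 9% | 8.4% to about 9% |
| ICC 0.05, THOPAS only (one set of 6000 runs) | 5.5% | 5.8% |
| ICC 0 (control, same set) | 5.1% | 5.1% to 5.2% |

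The ranges come from several simulations with slightly different therapist numbers and attrition. The 6.2% comes from only 2000 runs (Monte Carlo standard error about 0.5 points); the larger runs for Institution give 6.5% to 7.3%. With unequal caseloads (an assumed distribution), THOPAS-only clustering gave about 8% in both trials.

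**Step 4. Power once the test accounts for therapists.** Effective size per arm is the analysed number divided by V; unadjusted t-test, so baseline adjustment would add to it.
- Treatment, 99 per arm: V = 1.20 gives 89%; V = 1.40 gives 84%. At 1.54, 99/1.54 = 64.3, still at least the 64 required.
- Institution, 70 per arm: V = 1.20 gives 89%; V = 1.40 gives 84%. At 1.54, 70/1.54 = 45.5, still at least the 45 required.

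**The case against.** The strongest reply is that the authors did not overlook clustering. They sized both trials for it and name multilevel modelling inside the primary endpoint section. The article also refers details to a statistical analysis plan that is not shown, and that plan may settle the role of the multilevel model. This would be decisive if the article were merely silent. It is not: it states the terms of the primary model, and those terms omit the therapist. A later plan would have to change the stated model, not just add detail to it. What can properly be left to that plan is the exact random-effects structure and the degrees-of-freedom method.

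Second, 0.1 is a planning value borrowed from another study. This is fair: the excess is conditional on it, is about one percentage point or less at ICC 0.05 with THOPAS-only clustering, and vanishes at zero. But it is the value on which the plan justifies recruiting 40% more children.

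Third, the documents do not say that TAU children are free of clustering. The factor 1.4 is applied to both arms, and Treatment as usual allows psychotherapeutic care. This also stands, but it cuts the other way: THOPAS-only clustering gives the smaller excess.

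Fourth, the 8.2% and 11.4% figures use the 10% sample-size allowance as a variance multiplier, a use the plan does not state. They are best read as an indication, with 7.4% as the central figure.

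**Conclusion.** The concern holds: the primary analysis is wrong as written for ADOPT Treatment and ADOPT Institution. Under the plan's own ICC of 0.1 and five children per therapist, with clustering in THOPAS only, the stated ANCOVA has a two-sided type I error of about 7.4% by formula and roughly 6% to 7.6% in simulation, against a stated 5%. Unequal caseloads raise this to about 8%, and equally strong clustering in TAU to about 8.4% to 9.8% without unequal caseloads.

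The size rests on two things the article cannot settle: the therapist ICC that will actually occur and whether TAU care is clustered. The direction does not depend on them as long as the therapist ICC is above zero. ADOPT Online has no therapist contact and is not affected.

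**What to change.** For ADOPT Treatment and ADOPT Institution, name as the primary analysis a linear mixed model with the same fixed effects (baseline, study center, gender, arm) and a random therapist effect that acts only in the THOPAS arm, each TAU child forming its own cluster. Fit it by REML with Kenward-Roger or Satterthwaite degrees of freedom, since five children per therapist implies only about 23 therapists in Treatment (116/5) and 17 in Institution (83/5). If TAU children turn out to share identifiable providers, state in advance how that clustering enters. Keep the ANCOVA as a sensitivity analysis, and say that the mixed model decides if the two differ. ADOPT Online can keep the ANCOVA.

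The cost is a change of wording before unblinding and a therapist identifier for each THOPAS child. The identifier should be easy to supply, because therapists complete a protocol after every session (Treatment fidelity) and the multilevel modelling already announced needs it. No extra children are required: power stays at or above 80% at the planned analysed numbers.
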